## FOLLOW-UP

### Follow-up per Patient

Doppler sonography will be performed within the first 7 postoperative days.

### Duration of Intervention per Patient

All patients (both treatment and control groups) are treated with GCS from patient positioning until the fifth postoperative day, combined with subcutaneous administration of low-molecular-weight heparin, which is started with the first postoperative day and continued until discharge.

All trial-related investigations (intervention and follow-up) are limited to the single stay of each patient for their surgery. During the surgical procedure, IPC is applied. The primary end point (incidence of VTE) is then evaluated by Doppler sonography within 7 days after surgery (Table). No further follow-up is planned.

**TABLE. T1:** Trial-Related Investigations

Time point	Trial measure
Perioperatively	Graduated compression stockings
Surgical procedure	IPC (activated/not activated)
Starting on first postsurgical day	LMWH according to the specific standards of the respective center
Surgery to 7th postoperative day	Doppler-sonography: primary (incidence of VTE) and secondary end points
Surgery to 7th postoperative day	Assessment of safety

IPC, intermittent pneumatic compression; LMWH, low-molecular-weight heparin; VTE, venous thromboembolism.

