### Additional Treatments

In case of evidence of thrombosis or PE, drug therapy is initiated according to general practice guidelines as established by the respective center. If thrombosis is detected, compression therapy is also started accordingly.

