## SAFETY CONSIDERATIONS

### Assessment of Safety

Adverse events associated with IPC will be monitored and reported according to good clinical practice (GCP) principles and regulatory requirements. Assessment of safety does not constitute an end point of this study.

Our pilot study indicated that application of IPC during the surgical procedure is safe, and that it reduces VTE risk considerably.^18^ Previous studies have not reported any severe complications by use of IPC. For the proposed additional, exclusively intraoperative use, there is currently no evidence. The procedure is therefore not considered standard practice. Thus, it is not unethical to withdraw IPC from patients of the control group, which will receive medical care according to local standards. In addition, even patients of the control group will benefit from improved detection rates of VTE by the Doppler sonography each patient will receive (not part of standard clinical practice). Evidence on the efficacy of the easy-to-implement regimen would, however, significantly affect clinical care and ultimately benefit patients. An independent data safety monitoring board will closely review safety data on a regular basis and will make recommendations regarding further conduct of the trial, eg, to continue or hold enrollment, to amend protocol, or to stop the study early.

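### Planned safety assessment stops on postoperative day 7, the last day on which the trial's own scan can start drug therapy, so later in-hospital bleeding can go unrecorded

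*Protocol article*

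**What the plan says.** Five statements in the protocol article bear on this point.

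- **Safety window.** The Table under Duration of Intervention per Patient reads "Surgery to 7th postoperative day Assessment of safety". The text above it says "No further follow-up is planned".
- **Scan window.** Under Follow-up per Patient: "Doppler sonography will be performed within the first 7 postoperative days". The Assessment of Safety section adds that every patient receives this scan and that it is not routine care. It presents the better detection as a benefit to control patients.
- **Consequence of a positive finding.** Under Additional Treatments: "In case of evidence of thrombosis or PE, drug therapy is initiated according to general practice guidelines as established by the respective center".
- **Outer limit of the trial.** Under Duration of Intervention per Patient: "All trial-related investigations (intervention and follow-up) are limited to the single stay of each patient for their surgery". In the same section, LMWH prophylaxis is "started with the first postoperative day and continued until discharge".
- **Safety oversight.** Under Assessment of Safety: "Adverse events associated with IPC will be monitored and reported according to good clinical practice (GCP) principles and regulatory requirements", and "An independent data safety monitoring board will closely review safety data on a regular basis". Safety is not an end point.

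**The concern.** The scan is a trial procedure that can lead to treatment. Some thromboses will be found only because the trial looked for them, and some of those patients will receive drug therapy soon after a craniotomy. Bleeding is the obvious possible cost. The planned safety window closes on the last day on which the scan can start such therapy, so the later the scan, the less of the treated period is observed.

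What is at stake is the safety record and not the efficacy comparison. Because the plan expects more VTE in the control arm than in the IPC arm, exposure to this treatment would also be expected to differ by arm. That makes a complete in-hospital record more useful. The existing safeguards do not clearly close the gap: the monitoring sentence is directed at events linked to IPC, and the board can review only what is collected.

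**Working it through.** **Inputs.** From Sample Size: VTE rates of 24% (control) and 9% (IPC), two-sided alpha 5%, power 90%, 127 analysed and 146 recruited per group, dropout about 13%. From the Table and Follow-up per Patient: scan and safety assessment both end on postoperative day 7.

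**The plan's own figure.** For two proportions without continuity correction,

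n = [1.960·√(2·0.165·0.835) + 1.282·√(0.24·0.76 + 0.09·0.91)]² / 0.15² ≈ 126.6, rounded up to 127 per group.

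With dropout, 127 / 0.87 = 145.98, rounded up to 146. Both stated figures reproduce, and nothing below changes them.

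**Safety days left after a scan on day d: 7 − d.**

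| Scan day | 1 | 2 | 3 | 4 | 5 | 6 | 7 |
|---|---|---|---|---|---|---|---|
| Days left | 6 | 5 | 4 | 3 | 2 | 1 | 0 |

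**Patients with VTE at the planned rates.**

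- Analysed: 127 × 0.24 + 127 × 0.09 = 30.5 + 11.4 = 41.9, about 42 of 254.
- Recruited, if the same rates hold in dropouts: 146 × 0.24 + 146 × 0.09 = 35.0 + 13.1 = 48.2, about 48 of 292.

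**Share scanned late.** The protocol does not give it. As an assumed range, if 10% to 50% of the 42 were scanned on days 6 or 7, then 0.10 × 41.9 = 4.2 to 0.50 × 41.9 = 21.0 would have at most one day of safety assessment left. This counts all VTE cases, including those that would have been found and treated without the scan.

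**Why the count cannot be narrowed.** To contribute a bleed that goes unrecorded, a patient must be positive on a late scan, be treated by the centre, remain in hospital after day 7 and then bleed. Scan days, treatment rates for distal or muscle vein thrombosis, length of stay and bleeding risk are not given. All patients also receive LMWH until discharge, so only the bleeding risk added by treatment counts.

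**The case against.** The strongest defence is that the window suits the intervention. IPC is applied only during surgery, and seven days is a reasonable safety period for an intraoperative device. Therapy for a detected thrombosis is not randomised treatment. It follows centre practice, and patients stay under normal hospital care. This stands as a reason for low severity. It does not remove the point, because the trial adds the scan and the scan can trigger the therapy.

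A second defence is that an article condenses the full protocol, and that reporting periods for serious events and board listings usually sit in the protocol, a safety manual or a charter. That would excuse a missing detail. Here a window is stated, it ends on day 7, and the text plans nothing further. The defence does reduce certainty, since the row belongs to a short summary table.

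Several stronger readings are tempting, but the document does not support them.

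- *Bleeding is not recorded at all.* The monitoring sentence names only IPC-associated events, but the Table's safety row and the board's remit are general and may capture bleeding up to day 7.
- *The board does not see events by arm.* The document does not say what the board receives.
- *The scan-only cases can be counted.* A reader might subtract the 7.5% symptomatic rate in the Rationale section: 254 × 0.075 = 19.1, leaving 41.9 − 19.1 = 22.9, about 23 cases. That rate describes craniotomy patients in general and has no time window. Applying it to both arms pooled, dividing it between arms or spreading scan days evenly all rest on assumptions that the document does not support.
- *42 is a ceiling.* It covers analysed patients only; the figure for recruited patients is about 48.

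**Conclusion.** The point holds as a minor weakness in a stated window. Planned safety assessment ends on the last day on which the trial's non-routine scan can lead to drug therapy, so a late scan leaves little or no planned observation of the treatment it starts. The gap runs from day 7 to discharge and exists only for patients still in hospital then.

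About 42 of 254 analysed patients, or about 48 of 292 recruited, would have VTE if the planned rates of 24% and 9% hold. Only an unknown part of these would be found by the scan alone, late in the window, treated and still in hospital. The number of missed bleeds cannot be derived and is probably small.

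The primary comparison, the secondary end points and the sample size are unaffected. The common day-7 window for the end points is not in question.

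**What to change.** Change the safety row of the Table so that major and intracranial bleeding and other serious adverse events are recorded from surgery to postoperative day 7 or discharge, whichever is later. Adjust the sentence that rules out further follow-up to match. Take the events from existing hospital records and include them in the safety data that the board already reviews. Keep the day-7 window for the primary and secondary end points, and leave the scan and the treatment rules as they are.

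The cost is a short amendment and one discharge entry in the eCRF. No visit is added, and the change stays within the single-stay limit and the period of LMWH prophylaxis. The downside is that observation time will vary with length of stay, so safety rates should also be shown to day 7. Nothing is gained for patients discharged by day 7, and events after discharge remain uncollected.

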## DATA MANAGEMENT AND STATISTICAL ANALYSIS

### Methods Against Bias

Bias in assessment is addressed by a randomized single-blinded study design. Randomization will be stratified with respect to treatment center and will be performed centrally via an internet-based automatic system at the local Coordination Centre for Clinical Trials. The personnel performing Doppler sonography and diagnosis of PE will be blinded to group status of all patients; in addition, sonography will be performed according to Deutsche Gesellschaft für Ultraschall in der Medizin guidelines (Untersuchung der tiefen Beinvenen und Beckenvenen, Grundlagen und Technik).^19^ All ultrasound examiners involved in the study will meet and establish consensus on the definitions of DVT and its subtypes before the study starts. Patients are blinded to the randomization. To ensure this and to enable identical treatment in all patients of the treatment group, the same type of IPC device (Flowtron ACS900 (Arjo)) will be used in all centers taking part in the study. To avoid a center bias, all centers participating in the study will be limited to a maximum number of 100 patients over the duration of the study. However, the centers will be instructed to recruit their patients from a consecutive series to not introduce selection bias. As a consequence of this concept, there is a limit of 100 patients over the duration of the study per center despite the obvious ability of certain centers to contribute a higher number of patients.

The study will be analyzed according to the intention-to-treat principle to avoid attrition bias. It is registered prospectively in the DRKS (German Register of Clinical Studies; DRKS00034190) and will be reported according to CONSORT (Consolidated Standards of Reporting Trials).

### Statistical Analysis

The analysis of the primary end point will be performed by logistic regression using treatment group and treatment center as covariates because of the stratified randomization with respect to treatment center based on the intention-to-treat population. A per-protocol analysis will serve as sensitivity analysis. In addition, according to the very important covariate “duration of surgery” in the previous study^18^ (which could not be used as a stratification variable), an additional logistic regression using treatment group, treatment center, and duration of surgery as covariates will be performed as sensitivity analysis as well.

Analysis of binary secondary end points will be performed in the same way. All secondary variables will be analyzed in an exploratory manner. An interim analysis of the 2 VTE rates will be performed after recruitment of 50% of patients to adapt sample size if necessary (without analyzing futility or efficacy).

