## RATIONALE AND BACKGROUND INFORMATION

Venous thromboembolism (VTE) subsumes deep vein thrombosis (DVT) and pulmonary embolism (PE). Compared with other patient groups, neurosurgical patients are considered to be at an increased risk for these conditions. This is due to presence of malignancy, long duration of procedures, reduced mobility, and direct release of procoagulants such as tissue factors from brain tissue.^1-3^ Up to 50% of patients develop VTE after craniotomy.^4,5^ In the majority of cases, this condition is asymptomatic. However, symptomatic VTE occurs in 7.5% of patients undergoing craniotomy,^6-8^ and even asymptomatic VTE localized to distal muscle veins can progress to symptomatic deep vein thrombosis.^9-13^ This can lead directly and without clinical warning to PE in 7% of affected patients.^14^ Such a PE is caused by DVT in >90% of cases,^15^ occurs in 3.7% of all patients undergoing craniotomy, and is fatal in up to 50% of all affected neurosurgical patients.^5,13,16^ Thus, sufficient prophylaxis of VTE would considerably reduce unnecessary additional risks associated with neurosurgical procedures. Two different approaches have been described to achieve this: pharmacological prophylaxis, eg, by low-molecular-weight heparin (LMWH) or unfractionated heparin on the one hand, and mechanical prophylaxis by graduated compression stockings (GCS) or IPC on the other hand. With IPC, multichambered sleeves are positioned around the lower extremity and sequentially inflated to “milk” the blood from the veins, mimicking the physiological muscle pump. Most trials studying the effect of IPC have implemented this method for prolonged time intervals of several days after surgery; as a consequence of these long time intervals, poor compliance in using the devices has been reported as an issue in several publications.^17,18^

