### Sample Size

Sample size calculation for the comparison of the VTE rates in the treatment and control groups is based on a two-sided chi-square test with significance level alpha of 5% and a power of 90%. The pilot study^13^ showed a VTE incidence of 26% in the control group vs 7% in the treatment group. To avoid overoptimistic treatment effect assumptions, we assume VTE rates of 9% and 24% in the treatment and control groups, respectively. This results in 127 patients per treatment group. Assuming a similar dropout rate as in the previous study (approx. 13%), 146 patients per group (292 in total) will have to be recruited (Figure 1).

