### Outcome Measures

Primary end point:Incidence of VTESecondary end points:Proximal and distal deep vein thrombosis, symptomatic vs asymptomatic VTE, muscle vein thrombosis, central venous catheter–related thrombosis, PE, death, influence of lesion type, and duration of surgery.

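### The primary logistic model adjusts for centre only; adding a two-level preoperative lesion category would cheaply protect a valid comparison against chance imbalance, with a modest gain in power

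*Protocol article*

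**What the plan says.** The primary model is stated twice in the protocol article, under Sample Size and under Statistical Analysis: "The analysis of the primary end point will be performed by logistic regression using treatment group and treatment center as covariates". The reason given is that randomisation is stratified by centre, and Methods Against Bias names no other stratification factor. One further covariate model is described: "an additional logistic regression using treatment group, treatment center, and duration of surgery as covariates will be performed as sensitivity analysis as well". Lesion type appears in neither model.

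Three other places bear on lesion type:

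- Rationale and Background Information explains the raised VTE risk of neurosurgical patients: "This is due to presence of malignancy, long duration of procedures, reduced mobility", followed by release of procoagulants from brain tissue.
- Outcome Measures includes among the secondary end points "death, influence of lesion type, and duration of surgery".
- The single inclusion criterion is elective craniotomy for intracranial pathology, with no restriction by type of lesion.

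The trial is sized for a "two-sided chi-square test with significance level alpha of 5% and a power of 90" per cent. On the rates, "we assume VTE rates of 9% and 24% in the treatment and control groups, respectively".

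**The concern.** The lesion exists before randomisation, and intraoperative compression cannot change it. If malignancy predicts VTE within the craniotomy population, as the background section suggests, a term for it in the logistic model sharpens the treatment test and removes the part of the estimate that is due only to chance differences in case mix. Duration of surgery, the one extra covariate the article does use, is known only after randomisation.

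The trial's own history makes this relevant. The Discussion says that the pilot was weakened because a prognostic factor differed between randomised arms. Sample Size gives high priority to avoiding an underpowered trial, and calls the sample size conservative because logistic regression is said to be more powerful than the chi-square test. With centre as the only covariate, that advantage depends on centres differing in risk.

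At stake are a small amount of power and, in a minority of possible trials, a result that is hard to interpret because one arm had visibly more malignant lesions. The article names the covariates of the primary model, so this is not a detail left to a separate analysis plan.

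**Working it through.** **1. The plan's own sample size.** With rates 0.24 and 0.09, mean 0.165, two-sided 5% and 90% power, the uncorrected chi-square formula is

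n = [1.960·√(2·0.165·0.835) + 1.282·√(0.24·0.76 + 0.09·0.91)]² / 0.15² = (1.0288 + 0.6588)² / 0.0225 = 126.6, so 127.

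This agrees with the article: "This results in 127 patients per treatment group". Power at 127 per arm is 90.1%. Dropout: 127/(1 − 0.13) = 146 per arm, also as stated. Expected events among the 254 analysed: 254 × 0.165 ≈ 42.

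**2. Inputs the article does not give.** The share of malignant lesions and their odds ratio (OR) for VTE are assumptions, varied below.

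**3. Average power with and without lesion category.** Simulated trials had 127 per arm, five equal centres with no centre effect, and overall rates held at 24% and 9%. There were 4,000 runs per setting, with Wald tests from both models on the same data.

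| Malignant share | OR | Treatment + centre | + lesion category |
|---|---|---|---|
| 30% | 1.5 | 91.2% | 91.5% |
| 30% | 2 | 91.0% | 91.4% |
| 30% | 3 | 91.2% | 92.1% |
| 30% | 5 | 90.9% | 93.1% |
| 50% | 1.5 | 90.8% | 90.9% |
| 50% | 2 | 90.3% | 90.9% |
| 50% | 3 | 90.6% | 91.5% |
| 50% | 5 | 89.1% | 91.4% |

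A further set with shares of 40% and 60% and OR 2 to 4 gave gains of 0.5 to 1.5 points (for example 89.9% to 91.1% at 40% and OR 3). The gain is therefore about 0–1 point for OR up to 3 and about 2 points at OR 5. With no lesion effect (OR 1) it is nil. Simulated type I error was 4.2–5.3% without the covariate and 4.4–5.6% with it, so both are near 5%.

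In these runs, where centres do not differ in risk, treatment plus centre had practically the same power as the chi-square test (90.6% against 90.5% at 50% and OR 3).

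**4. How often the arms differ.** The standard deviation of the between-arm difference in share q is √(2q(1 − q)/127).

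- q = 30%: 5.8 points; chance of a gap of 10 points or more about 8%.
- q = 40% or 60%: 6.1 points; about 10%.
- q = 50%: 6.3 points; about 11% (about 12% simulated).

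**5. What a 10-point gap does to the risk difference at OR 3.**

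- Share 40%, overall risk 16.5%: solving 0.6·p0 + 0.4·p1 = 0.165 gives p0 = 10.4% and p1 = 25.7%. Shift: 0.10 × 15.4 = 1.5 points.
- Share 50%, control-arm risk 24%: p0 = 14.4% and p1 = 33.6%. Shift: 0.10 × 19.2 = 1.9 points.

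**6. Power given such a gap.** With a 40% share overall, 127 per arm, 3,000 runs per setting, and 10 points more malignancy in the compression arm, power without adjustment is about 87% (OR 2), 84–85% (OR 3) and 83% (OR 4). With adjustment it is 91–92% in all three. With the gap reversed, unadjusted power rises to 94–97% while adjusted power stays at 90–93%. Unadjusted, the imbalance can therefore work against the device or flatter it.

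**The case against.** The strongest reply is that nothing in the plan is wrong. The comparison is randomised, the one stratification factor is in the model, and type I error is held. A shift of 1.5 points is about a third of the standard error of the risk difference, √(0.24·0.76/127 + 0.09·0.91/127) = 4.6 points, and a tenth of the assumed 15-point effect. Taken over all trials, such variation is already covered by the test's error rate. The covariate the protocol itself calls very important is duration of surgery, and that has a named sensitivity model. All of this stands. It limits the point to an improvement, but it does not remove the benefit in a trial that does turn out imbalanced.

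Several stronger readings are tempting, and the article does not support them:

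- A reader might infer that lesion type is already on record at randomisation. The article lists its influence as a secondary end point and does not say when or how it is captured. It could come from histology after surgery.
- A reader might equate lesion type with malignancy. The article does not define the categories.
- A reader might take malignancy as the leading predictor because it comes first in the list. That sentence compares neurosurgical with other patients and gives no ranking or effect size among craniotomy patients.
- A reader might conclude that substantial power is being given away. The gain is small and rests on assumed inputs.

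It is also fair to say that odds ratios are non-collapsible, so adding a prognostic covariate changes the odds ratio being estimated. That is a cost to declare, not a reason against adjustment.

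**Conclusion.** The point holds as a modest, low-cost improvement to a valid primary analysis. Adjusting for a two-level lesion category adds roughly 0–2 points of power for assumed malignant shares of 30–60% and odds ratios of 1.5–5. The 90% design is not in danger without it.

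The better argument is robustness. About one trial in ten would show a gap of 10 points or more in lesion share, half of these in each direction. At an odds ratio of 3 an unadjusted analysis would then be several points of power worse or better than designed, while the adjusted one stays close to plan. If malignancy does not predict VTE among craniotomy patients, there is no gain and almost no loss. The figures assume no difference in risk between centres and a correctly classified lesion category; misclassification would shrink the benefit.

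**What to change.** In both places where the primary model is stated (Sample Size and Statistical Analysis), pre-specify logistic regression with treatment group, centre and a two-level lesion category, malignant versus non-malignant. Define the category by the preoperative diagnosis, recorded before randomisation, and say explicitly that postoperative histology does not alter it. Keep the treatment-plus-centre model as a sensitivity analysis. The exploratory evaluation of lesion type as a secondary end point can stay as it is.

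The costs are:

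- one preoperative field in the electronic case report form;
- one more parameter with about 42 expected events, which is why the category should have only two levels;
- some misclassification of the preoperative diagnosis;
- a treatment odds ratio that is conditional on lesion category as well as centre, which the report should state.

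Trial Status describes the study as not yet implemented, so the change can be made before any outcome is known. The same adjustment chosen after unblinding would carry much less weight.

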**DISCUSSION::**

If this trial shows that intraoperative IPC reduces the risk of VTE to the extent observed in our pilot study (number needed to treat: 5.24), the potential benefit to neurosurgical patients would be significant. The results would potentially influence treatment guidelines by providing the high-quality evidence needed to make robust recommendations.

ABBREVIATIONS:DRKSDeutsches Register Klinischer StudienDVTdeep vein thrombisisGCPgood clinical practiceGCSgraduated compression stockingsLMWHlow-molecular-weight heparinVTEvenous thromboembolism.

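### The centre-adjusted logistic model is prescribed for every binary secondary end point, with no fallback for those, above all death, that may have no events in one arm

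*Protocol article*

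**What the plan says.** Under Statistical Analysis, the protocol article fixes the primary model: "The analysis of the primary end point will be performed by logistic regression using treatment group and treatment center as covariates". It extends that model to the rest in one sentence: "Analysis of binary secondary end points will be performed in the same way". The next sentence limits the claim: "All secondary variables will be analyzed in an exploratory manner".

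Under Outcome Measures, the secondary end points include "central venous catheter–related thrombosis, PE, death, influence of lesion type, and duration of surgery". The article gives no exception for rare events and no expected rates for these end points in the trial. The only anchors are in Rationale and Background Information: PE "occurs in 3.7% of all patients undergoing craniotomy", and it is said to be fatal in up to half of affected neurosurgical patients.

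**The concern.** The model suits the primary end point, where events are plentiful. The same model is prescribed for end points where only a handful of events can be expected.

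If one arm has no events, the likelihood keeps rising as the treatment coefficient moves towards plus or minus infinity. Software then either fails to converge or prints an extreme odds ratio with an enormous Wald interval. If both arms have events but few in total, the estimate exists, but it is biased away from 1 and its interval relies on large-sample theory that does not hold.

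PE and its fatality are the harms the article uses to motivate prophylaxis. If the prescribed model fails on them, the analyst has to choose a replacement after seeing the data. A sentence written now avoids that.

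**Working it through.** **The plan's own figure.** Sample Size: "we assume VTE rates of 9% and 24% in the treatment and control groups, respectively", with a "two-sided chi-square test with significance level alpha of 5% and a power of 90" per cent. With mean rate (0.09 + 0.24)/2 = 0.165:

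n = [1.960·√(2·0.165·0.835) + 1.282·√(0.09·0.91 + 0.24·0.76)]² / 0.15² = 126.6, so 127 per group.

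127/0.87 = 146 to recruit. Both figures reproduce.

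**When the treatment odds ratio is not finite.** In a model with treatment and centre terms, with patients free of the event in both arms of every centre, the treatment estimate is finite if and only if each arm has at least one event somewhere in the trial. The quantity needed is therefore

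P(empty arm) = (1 − p_C)^n + (1 − p_T)^n − (1 − p_C)^n·(1 − p_T)^n, with n = 127.

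**Inputs.**
- PE rate 3.7% (Rationale and Background Information).
- Fatal PE at most 3.7% × 50% = 1.85% (same section).
- Effect: either none, or (an assumption) the ratio planned for VTE, 9/24 = 0.375, applied to a control rate equal to the figure shown.
- 1% is an assumed rate for a rarer end point. The article gives no rate for catheter-related thrombosis or for death from all causes.

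| End point | p_C | p_T | Expected events | P(empty arm) |
|---|---|---|---|---|
| PE, no effect | 3.7% | 3.7% | 9.4 | 1.7% |
| PE, ratio 9:24 | 3.7% | 1.39% | 6.5 | 18% |
| Death at the fatal-PE ceiling, no effect | 1.85% | 1.85% | 4.7 | 18% |
| Death at that ceiling, ratio 9:24 | 1.85% | 0.69% | 3.2 | 47% |
| Assumed 1%, no effect | 1% | 1% | 2.5 | 48% |
| Assumed 1%, ratio 9:24 | 1% | 0.375% | 1.7 | 73% |
| VTE (primary) | 24% | 9% | 41.9 | essentially 0 |

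Example, fourth row: 0.9815^127 = 0.093 and 0.99306^127 = 0.413, so 0.093 + 0.413 − 0.093·0.413 = 0.468.

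Vital status may be known for all 146 randomised per arm. With n = 146 the two death rows become 0.066 + 0.066 − 0.066² = 13%, and 0.066 + 0.362 − 0.066·0.362 = 40%. The conclusion does not change.

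**Centres without events.** The cap of 100 patients per centre implies at least 3 centres for 292 patients. The actual number is not given. With K equal centres (an assumption), P(at least one centre without PE at 3.7%) = 1 − [1 − 0.963^(254/K)]^K, which is 12%, 55% and 94% for K = 3, 5 and 8. In such a centre only the centre coefficient diverges. Illustration: 5 centres of 50 patients, 7 versus 3 events, one centre empty. The treatment odds ratio is 0.41 (95% CI 0.10 to 1.64) whether the empty centre is kept in the model or left out. Its patients add nothing to the estimate, but the estimate stays finite.

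**The case against.** Much of the case on the other side stands.

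- **The analyses are exploratory.** No confirmatory claim depends on them, and counts per arm can be reported under any model. The PE and death results would not be lost. This limits the weight of the point.
- **PE is mostly estimable.** At 3.7% the odds ratio is finite in about 82% to 98% of trials. A reader might infer that PE will often have no estimate. The article's own rate does not support that. What remains for PE is poor inference on 6 to 9 events.
- **Empty centres do not break the treatment estimate.** A reader might take the high chance of a centre without events as the chance that the model fails. It is not, as shown above.
- **Rates for death and catheter thrombosis are not given.** The 1.85% is a ceiling for fatal PE only. Deaths from other causes would raise the total, and fewer fatal PEs would lower it. PE is also sought by CT only on clinical suspicion and only within the hospital stay, so observed PE may be rarer than 3.7%.
- **Logistic regression need not mean unpenalised maximum likelihood, and sparse-data detail often sits in the SAP.** This is true in part: Firth's method would fit the wording. However, the article makes a positive choice for all binary secondary end points and ties it to the primary model. It is this choice that suits the rare end points badly.

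A reader might also infer that the trial will report only odds ratios and so cannot be set against the pilot's number needed to treat of 5.24. The documents do not support this. The article names no effect measure and excludes none. A risk difference follows from the two rates, or from the same model by standardisation, and the choice of summary measure is commonly left to the SAP. The trial is also planned on 9% versus 24% (1/0.15 = 6.7), not on confirming 5.24.

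**Conclusion.** The point holds as a limited one. The stated rule sends very rare binary end points through a model that cannot give a finite treatment odds ratio when an arm has no events. For death at the article's ceiling for fatal PE, that is about 18% of trials (no effect) to 47% (1.85% in controls, ratio 9:24 assumed). For PE at 3.7% it is about 2% to 18%. For an end point at an assumed 1% it is about half or more.

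These figures rest on 127 analysed per arm, on background rates carried over to this trial, and on an assumed effect on PE and death. They do not depend on the number of centres. The primary analysis is sound in this respect.

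**What to change.** Under Statistical Analysis, qualify the sentence on binary secondary end points. For example: where a binary secondary end point has fewer events than a prespecified minimum, or no events in either arm, counts per arm will be reported together with one of the following, named in advance, in place of the ordinary model:

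- Firth-penalised logistic regression on treatment group and centre, with a profile-likelihood interval; or
- a centre-stratified Mantel-Haenszel risk difference with an interval suited to small counts.

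The trial statistician should set the minimum count before any outcome data by arm are seen; the documents give no basis for a particular number. If an end point has no events in either arm, counts alone are enough.

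The cost is one or two sentences and a few lines of code, with no change to patients, data or sample size. The article describes the trial as not yet implemented, so the change can be made without touching accrued data.
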